#### Recruitment {15}

The participants will be recruited within the two existing HDSS in Nouna, Burkina Faso, and in Siaya, Kenya. The recruitments will be conducted by the Health Research Center (CRSN) in Nouna and by the Kenya Medical Research Institute (KEMRI)-Kisumu. These institutions have long-standing expertise in conducting demographic and health surveys in the target populations, including community sensitization and data collection. For each study site, we will establish a sampling frame of 2000 households with children below 5 years of age and within a 5- or 10-km radius of local weather stations, respective of study site. These households will be selected with a probability proportional to population size (PPS), according to the latest census. Of these, we will recruit 600 households at each study site with children who fulfill the eligibility criteria.

### Assignment of interventions: allocation

#### Sequence generation {16a}

At each site, the main data manager of the baseline survey will produce a computer-generated sequence of households stratified by the 5 weather stations. Using PPS, the households will be randomized into either the intervention group or the control group.

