### Interventions

#### Explanation for the choice of comparators {6b}

For the allocation of intervention arms, we apply simple randomization, treating the households as intervention clusters. At each site, the main data manager of the baseline survey produces a computer-generated sequence of households that are allocated to either the intervention group or the control group, applying the PPS approach. The implementation partners for home gardens (DEZLY Consulting, the Nouna Agricultural Service and CABE) and the lead dieticians for nutrition counseling use these lists of randomized households to implement the intervention components. As this is a behavior change trial, blinding the participants and or the implementation team is not possible.

All participating households in the ALIMUS trial benefit from trimonthly follow-up visits by a research study team (not Community Health Volunteers (CHVs). During these follow-up visits, the study team takes anthropometric measures and examines iron and zinc status of the target child. We also assess signs and symptoms of clinical malaria and provide diagnostic tests if a child has fever, shivers, a headache, or diarrhea. In case of sickness, the child and the caregiver are referred to the nearest health care facility for appropriate treatment. For the control group, we provide standard information on healthy feeding practices. This comprises one group counseling session on the Essential Nutrition Action (ENA) messages, but no tailored individual sessions afterwards. During the group counseling, we hand-out an information leaflet corresponding to the ENA messages.

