#### Methods for additional analyses (e.g., subgroup analyses) {20b}

In addition to adjustments, we will perform difference-in-difference (DID) analyses to control for unmeasured confounding. These DID estimates compare the change in outcome variables from endline to baseline examinations between the intervention and the control group [41]. Also, we will conduct sub-group analysis according to age group of the children and by location of the weather station.

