## Abbreviations

ABC: Activity-based costing
CABE: Centre for African Bio-Entrepreneurship
AFPQ: African Food Propensity Questionnaire
CGHR: Centre for Global Health Research
CH_4_: Methane
CHEERS: Consolidated Health Economic Evaluation Reporting Standards
CHV: Community Health Volunteer
CO_2_: Carbon dioxide
cRCT: Cluster-randomized controlled trial
CRSN: Centre de Recherche en Santé de Nouna
CSO: Consulting service organization
DDS: Dietary Diversity Score
DEval: German Institute for Development Evaluation
DFG: German Research Foundation
DID: Difference-in-differences
ENA: Essential Nutrition Action
FVS: Food variety score
GRT: Group- or cluster-randomized trials
HAZ: Height-for-age *z*-score
Hb: Hemoglobin concentration
HDSS: Health and Demographic Surveillance System
HFIAS: Household Food Insecurity Access Scale
HHS: Household Hunger Scale
HIGH: Heidelberg Institute of Global Health
HIV: Human immunodeficiency virus
HKI: Helen Keller International
ICC: Intra-class correlation coefficient
IPCC: Intergovernmental Panel on Climate Change
IQR: Interquartile range
IYCF: Infant and Young Child Feeding
KEMRI: Kenya Medical Research Institute
LMICs: Low- and middle-income countries
MAD: Minimum acceptable diet
MAR: Mean adequacy ratios
MDD: Minimum dietary diversity
MMF: Minimum meal frequency
N_2_O: Nitrous oxide
NGO: Non-governmental organization
NIH: National Institutes of Health
PCA: Principal component analysis
PI: Principal investigator
ppm: Parts per million
PPS: Probability proportional to population size
SD: Standard deviation
SERU: Scientific and Ethics Review Unit
SOPs: Standard Operating Procedures
WAZ: Weight-for-age *z*-score
WBCs: White blood cells
WHZ: Weight-for-height *z*-score
WHO: World Health Organization

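### Allocation is described as simple, as stratified by weather station and as PPS; with 300:300 fixed per site these cannot all be true, and one scheme should be stated

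*Protocol article*

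**What the plan says.** The protocol article describes allocation in two places.

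- Explanation for the choice of comparators {6b}: "For the allocation of intervention arms, we apply simple randomization, treating the households as intervention clusters". The next sentence has the data manager produce a computer-generated list of households "allocated to either the intervention group or the control group, applying the PPS approach".
- Sequence generation {16a}: the data manager produces a "computer-generated sequence of households stratified by the 5 weather stations", followed by "Using PPS, the households will be randomized into either the intervention group or the control group".

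Four other places bear on the reading.

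- Trial design {8} and Participant timeline {13} fix 300 intervention and 300 control households at each site.
- Recruitment {15} uses PPS to build the sampling frame: "These households will be selected with a probability proportional to population size (PPS), according to the latest census". The abbreviation list has "PPS: Probability proportional to population size".
- Statistical methods {20a} models HAZ by multi-level linear regression, separately by site. The arm is the only named independent variable, with general adjustment for baseline imbalance. The levels are not named.
- Additional analyses {20b} is the only analysis section that mentions the stations: "Also, we will conduct sub-group analysis according to age group of the children and by location of the weather station".

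**The concern.** Unqualified simple randomisation has no strata and does not fix the arm sizes. Stratified randomisation does have strata. PPS draws units with unequal probabilities and is not a way of making a 1:1 assignment. A reader therefore cannot tell from the article how households came to be in one arm or the other.

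Two things depend on the answer. The first is whether every household had the same chance of intervention, which is what the unweighted intention-to-treat comparison assumes. If the chance rose with household or village size and the analysis ignored this, the arms would differ systematically in something that may be related to child growth. The second is whether the five stations were strata. If so, the primary model should reflect them.

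**Working it through.** **1. Does simple randomisation fit the fixed arms?** Inputs: 600 households per site, 300 per arm (Trial design {8}); five stations (Sequence generation {16a}). Assumption: an independent 1:1 draw for each household.

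- SD of arm size = √(600 × 0.5 × 0.5) = 12.2; 95% range for one arm 276 to 324.
- P(exactly 300) from Binomial(600, 0.5) = 0.0326, or 3.3%.
- With equal stations (assumed), 600/5 = 120 households each. The 95% range for one arm in a station is 49 to 71, and a split of 70:50 or worse has probability 2 × P(X ≤ 50) = 0.082.

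So literal simple randomisation fits neither the fixed 300:300 nor a stratified list.

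**2. What would literal PPS assignment do?** The article does not say which size would be used, so this is an illustration with household size. Mean sizes follow from Study setting {9}: 115,000/14,000 = 8.2 persons in Nouna and 220,000/54,869 = 4.0 in Siaya. Assumptions not in the article: a skewed size distribution around those means (2 plus a negative binomial), and a HAZ slope of −0.01 to −0.05 per additional person. In simulation, 300 of 600 households were drawn into the intervention arm with chance proportional to size.

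| Site | Intervention minus control, persons | Bias in HAZ, slope −0.01 to −0.05 |
|---|---|---|
| Nouna | about 2.9 | −0.03 to −0.14 |
| Siaya | about 1.0 | −0.01 to −0.05 |

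The planned effect is 0.18 to 0.25 HAZ (Sample size {14}). If PPS only sets how many households come from each village or station, with 1:1 assignment inside it, the bias is zero.

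**3. What would leaving out the strata cost?** First the plan's own sample size, with SD = 1 and two-sided alpha assumed, and design effect 1 + (2 − 1) × 0.05 = 1.05:

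households per arm = 2 × ((1.96 + 0.84)/δ)² × 1.05 / 2

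This gives 132 for δ = 0.25 and 255 for δ = 0.18. The plan states 135 and 260, so its figures are reproduced to within 3%. At 300 households per arm, power is 86% for 0.18 and 99% for 0.25.

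Then a simulation with five equal stations, exact 1:1 within station, 3,000 runs and δ = 0.18. The station share of HAZ variance is assumed. Monte Carlo error on the type I rate is about ±0.008.

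| Station share | Type I, strata out | Type I, strata in | Power, strata out | Power, strata in |
|---|---|---|---|---|
| 1% | 0.046 | 0.048 | 0.868 | 0.870 |
| 2% | 0.045 | 0.048 | 0.862 | 0.866 |
| 5% | 0.040 | 0.046 | 0.860 | 0.876 |
| 10% | 0.038 | 0.055 | 0.854 | 0.893 |

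Omission tends to be slightly conservative and costs 0.2 to 3.9 points of power.

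**The case against.** The strongest reply is that this is loose wording about a sound procedure. Recruitment {15} uses PPS correctly, and fixed 300:300 arms imply 1:1 overall. A plain reading is that PPS set the numbers per village or station and that assignment inside them was equal. Stratification and PPS-determined numbers are compatible. A randomly ordered list cut at 300 is often called simple randomisation, and the 3.3% applies only to a coin toss per household. Even then, 276 to 324 in one arm is chance imbalance, which causes no bias and barely affects power.

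Most of this stands. The binomial figures show only that the word simple does not fit; they do not measure harm. A reader might infer that PPS allocation has biased the arms. The documents do not support that: no section says a household's chance of intervention depended on its size, and the bias figures rest on an assumed slope and size distribution. A reader might also infer that the strata have been excluded from the primary model. Statistical methods {20a} is silent on this and does not name its levels, and the analysis plan is not shown, so exclusion is not established.

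The contradiction itself remains. Simple in {6b} and stratified in {16a} are both current text, and PPS is attached to arm assignment in both sections, so it is not a single slip. An unseen analysis plan does not remove a conflict between two statements that the protocol itself makes.

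**Conclusion.** The stated allocation rules conflict and need correction. The firm part is that simple, stratified and PPS cannot all describe the assignment of a fixed 300:300 per site. The consequence for bias is conditional: none if PPS is a misplaced sampling term, which is the likelier case. If PPS really set the assignment probabilities and was ignored in the analysis, the illustration gives −0.01 to −0.14 HAZ under the assumptions above. If station was a stratum and is left out of the model, the treatment estimate is still unbiased; the loss is about 0 to 4 points of power for assumed station shares of 1 to 10%. The sample size is unaffected.

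**What to change.** 1. Check the Stata allocation code that was run (Concealment mechanism {16b}); Trial status says randomisation is complete. State one scheme in both {6b} and {16a}: whether it was stratified by station, the ratio within station, and any blocking or exact split. If 1:1 within weather station is what was run, say so.
2. Confine PPS to the sampling step in Recruitment {15}.
3. If station was a stratum, include the five stations as fixed effects in the site-specific primary model.
4. Only if the code shows unequal assignment probabilities, report them and account for them in the intention-to-treat analysis, for example by weighting or by adjusting for the size variable.

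The cost is a check of existing code, corrected wording, and 4 model degrees of freedom per site. The sample size and field procedures do not change.

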#### Concealment mechanism {16b}

Study beneficiaries are selected through randomization via Stata using computer-generated random numbers. There is no human involvement, and the process is fully concealed from both study investigators and prospective participants during baseline measurements and until the study arm is assigned.

#### Implementation {16c}

Based on the randomization, the field supervisor will allocate the households to the intervention groups. The study group will be revealed at the same time to the participating households, the implementation team, and the field agents.

### Assignment of interventions: blinding

#### Who will be blinded {17a}

As this is a behavior change intervention, neither blinding of the participants nor of the implementation team is feasible. The data analysts will be blinded.

#### Procedure for unblinding if needed {17b}

The study design is openly labeled, and so, unblinding will not be possible.

### Data collection and management

#### Plans for assessment and collection of outcomes {18a}

Two quantitative surveys are conducted at baseline and endline of the ALIMUS trial. These surveys comprise questionnaire-based interviews on demographic and socioeconomic characteristics, medical history, dietary information, anthropometric measurements, micronutrient status through hand-held spectrometry, body temperature, and laboratory measurements for hemoglobin concentration (Hb) and malaria diagnosis. All project personnel are thoroughly trained and work according to Standard Operating Procedures (SOPs). The study team consists of field agents who conduct the questionnaire-based interviews and anthropometric examinations; laboratory technicians who perform the blood sample collection, body temperature and Hb measurements, hand-held spectrometry and malaria diagnosis; and a monitoring team who document monetary and opportunity costs of the intervention, knowledge gain, training and counseling activities, and garden yields. The data collection instruments and variables measured are presented in Table 2.

**Table 2 Tab2:** Variables measured and data collection instruments in the ALIMUS trial

Module	Measure/variable	Questionnaire/instrument
**Demographic**	Age (months), sex (male/female), mother’s age (years), mother’s ethnicity (categorical), mother’s religion (categorical)	Questionnaire
**Socioeconomic**	1. Mother’s education (categorical), mother’s occupation (categorical), mother’s marital status (categorical) 2. Number of people in the household (continuous) 3. Type of housing (roof, wall, ground), access to and type of water source (categorical), access to and type of toilet and electricity (categorical), availability of 14 household assets (yes/no), availability of 9 animals (yes/no) 4. Main source and amount of income (categorical and continuous), main type and amount of household expenditures (categorical and continuous)	1. Questionnaire 2. Questionnaire 3. Questionnaire 4. Questionnaire
**Diet**	1. Breastfeeding (starting age, ending age) 2. Complementary feeding (starting age) 3. Usual food intake	1. Questionnaire 2. Questionnaire 3. African-specific Food Propensity Questionnaire (AFPQ)

For laboratory examinations, we collect capillary blood samples of children. Hb is measured by hand-held photometer, and malaria parasites are microscopically identified on Giemsa-stained (4%, 30 min, pH 7.2) thick blood films. We calculate parasite density by examining microscopy fields corresponding to 400 white blood cells (WBCs), assuming an average WBC count of 8000/μL. Asymptomatic malaria is defined as the absence of fever (< 37.5 °C) and the presence of any Plasmodium spc.; clinical malaria denotes any parasite density plus fever (≥ 37.5 °C) or a history of fever within the last 48 h; and severe malaria is defined according to WHO criteria [40].

For the process monitoring, we employ tracking cards to document project inputs and activities, including equipment and seeds, garden trainings, and nutrition counseling sessions. In addition, the extension officers record the horticultural outputs in garden diaries. We conduct in-depth interviews and apply a deductive analysis strategy using pre-defined knowledge categories for home gardening and child feeding practices.

#### Plans to promote participant retention and complete follow-up {18b}

Adherence to the intervention will be supported through regular contacts to the beneficiaries during training sessions on home gardening and individual nutrition counseling. We will closely monitor the uptake of inputs such as seeds and garden tools, as well as the participation in all sessions.

#### Data management {19}

The data will be collected on tablets using the data entry software SurveySolutions (version 21.09, World Bank). The data will be checked daily by the field supervisors and weekly by the principal investigator. We ensure high data quality through regular de-briefings on the data collection and data entry procedures. The collected data will be stored securely as password-protected files (encrypted storage devices) and will be ultimately stored on the institutional cloud server at the Heidelberg Institute of Global Health (HIGH), Germany.

#### Confidentiality {27}

We ensure complete confidentiality of the data. Informed consent forms, laboratory books, and other participant-related documents will be safely stored during study conduct at the HDSS research centers in Burkina Faso and Kenya. All data and samples will be pseudonymized for analysis. The research data will be stored securely and password-protected throughout the data collection and processing stages. A digital exchange platform (secured and encrypted) at the Heidelberg University Computing Center will be used for the ALIMUS trial. All data collected will be stored in Microsoft-SQL databases that have been designed based on the Reference Demographic Surveillance Data Model, facilitating productive cross-collaboration efforts. According to the rules of good scientific practice, research data of this project will be archived for at least 10 years.

#### Plans for collection, laboratory evaluation, and storage of biological specimens for genetic or molecular analysis in this trial/future use {33}

No genetic or molecular analysis of biological material is planned in this trial.

#### Interim analyses {21b}

No interim analyses will be conducted. The results will only be analyzed at the end of the intervention (after 1 year).

#### Methods for additional analyses (e.g., subgroup analyses) {20b}

In addition to adjustments, we will perform difference-in-difference (DID) analyses to control for unmeasured confounding. These DID estimates compare the change in outcome variables from endline to baseline examinations between the intervention and the control group [41]. Also, we will conduct sub-group analysis according to age group of the children and by location of the weather station.

#### Methods in analysis to handle protocol non-adherence and any statistical methods to handle missing data {20c}

We will conduct per protocol analysis and compare it the intention-to-treat analysis.

#### Plans to give access to the full protocol, participant level-data, and statistical code {31c}

The data can be made available by the principle investigators for research purposes only, upon an agreed analysis proposal, and after signing a data transfer agreement.

### Oversight and monitoring

#### Composition of the coordinating center and trial steering committee {5d}

This is a multi-center study designed and coordinated by three institutions: HIGH, Heidelberg University, Heidelberg, Germany; CRSN, Nouna, Burkina Faso; and KEMRI, Kisumu, Kenya. The trials are performed in the Nouna HDSS area, Burkina Faso, and in the Siaya HDSS area, Kenya. Day-to-day support for the trial is provided by one principal nutrition counselor and two home garden officers, respectively. They run daily debriefings with CHVs as well as with garden leaders. The principal nutrition counselors and the home garden officers are also the contact persons for the on-site finance officers of the local partner organizations. The finance officers at CABE and DEZLY are responsible for procurement of inputs and equipment for the home garden component, while the finance officers at CRSN and KEMRI take care of the procurement of research equipment and consumables and the payment of research personnel. The trial steering committee consists of three investigators, representing one of the three research institutions as well as two coordinating scientists, who virtually meet in bi-weekly intervals for overall management and trouble-shooting.

#### Composition of the data monitoring committee, its role and reporting structure {21a}

A formal data monitoring committee (DMC) was not established as this is a low-risk intervention. However, each of the three research institutions allocates one independent data manager. This data manager will conduct plausibility checks, data cleaning, and analysis. The sponsors play no role in data management, analysis, and interpretation of findings. Thus, the data managers have no competing interests. During bi-weekly meetings, data managers will report their observations from plausibility checks and interim analysis to the steering committee.

#### Adverse event reporting and harms {22}

The implementation teams at each study site are equipped with monitoring tools to document referrals to the nearest health facility and the reasons for referral. We also capture reasons for lost to follow-up, including deaths.

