#### Participant timeline {13}

At both study sites, each participant is followed-up for at least 1 year, with a possible extension of an additional year (Table 1). After community sensitization, eligibility screening and consent taking, we perform baseline examinations over the course of 3 months. We then randomize households and allocate them to either the intervention group (*n* = 300 at each site) or the control group (*n* = 300 at each site). In groups of 20 beneficiaries, the intervention group participants receive trainings in setting up their gardens by their respective garden leader and counseling sessions on healthy child feeding practices by CHVs. Every 2 months, garden leaders and CHVs actively visit the intervention households for guidance on home garden practices and individual dietary counseling. In 3 month intervals, we integrate anthropometric measurements and assessments of micronutrient status and clinical malaria into this schedule. After the first 6 months of the intervention, refresher trainings of the beneficiaries for home garden practices are conducted in the form of group sessions. After another 6 months (1 year since start), we conduct endline examinations for the primary and secondary outcomes among all study participants. In addition, we monitor inputs and outputs according to the three major impact pathways throughout the intervention phase.

**Table 1 Tab1:** Activity timeline for the ALIMUS trial in rural Burkina Faso and Kenya

Time point	2021						2022												2023			
	Q3			Q4			Q1			Q2			Q3			Q4			Q1			Q2

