#### Frequency and plans for auditing trial conduct {23}

The steering committee and informal data monitoring team meet online bi-weekly to review the conduct of the trial. This includes the review of adherence to intervention components, logistical aspects, feedback from beneficiary households, completeness and quality of collected data, and adherence to milestones. Also, regular exchange about the trial progress is assured via phone calls and short messages.

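### Referrals are logged by the implementation teams, who meet intervention households far more often than controls, so referral counts from this log are likely to be ascertained unequally by arm

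*Protocol article*

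**What the plan says.** Item {22} (adverse events and harms) has two sentences. The first assigns the referral record: "The implementation teams at each study site are equipped with monitoring tools to document referrals to the nearest health facility and the reasons for referral". The second adds: "We also capture reasons for lost to follow-up, including deaths". It names no recorder and no arm.

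Item {22} does not define the implementation teams, but other sections indicate who they are. On the allocation lists, item {6b} says: "The implementation partners for home gardens (DEZLY Consulting, the Nouna Agricultural Service and CABE) and the lead dieticians for nutrition counseling use these lists". Item {16c} names the implementation team separately from the data collectors: "The study group will be revealed at the same time to the participating households, the implementation team, and the field agents".

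Contact with these staff differs by arm. For the intervention arm, item {13} says: "Every 2 months, garden leaders and CHVs actively visit the intervention households for guidance on home garden practices and individual dietary counseling". For the control arm, item {6b} says: "This comprises one group counseling session on the Essential Nutrition Action (ENA) messages, but no tailored individual sessions afterwards".

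A contact common to both arms is also described in item {6b}: "All participating households in the ALIMUS trial benefit from trimonthly follow-up visits by a research study team (not Community Health Volunteers (CHVs". At these visits sick children are referred to a health facility. In Table 1, the two rows labelled 3-monthly (micronutrients and malaria) carry footnote b, which restricts them to Kenya. The anthropometry row is marked only around baseline and endline.

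**The concern.** Read literally, item {22} places the referral log with delivery staff. A sick child in an intervention household has repeated chances of being noticed and logged by them, while a sick child in a control household has almost none. The protocol describes a research team that sees both arms and refers sick children, but does not say that its referrals reach the log.

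With equal true morbidity, such a log would show more referrals in the intervention arm. A neutral programme could look harmful, and a real harm could not be separated from closer observation. No formal data monitoring committee was set up, on the ground that the intervention is low-risk. Referral counts that depend on contact frequency are weak evidence for or against that premise. The primary HAZ analysis is not affected.

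**Working it through.** The plan states no figure on this point, so there is none to reproduce. The check counts scheduled contacts per arm and then asks what unequal contact would do to the log if true morbidity were equal.

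**Inputs from the protocol**
- Intervention arm: one group counselling session, then individual counselling every 2 months. Table 1 marks 10 months for the individual sessions. Item {13} adds garden-leader visits every 2 months.
- Control arm: one group session and no individual sessions (item {6b}).
- Research team: a visit every 3 months to all households (item {6b}), so 12/3 = 4 in a year.

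**Implementer contacts over 12 months, leaving out group garden trainings**
- Intervention, low count (CHV and garden leader counted as one visit, Table 1 months): 1 + 10/2 = 6.
- Intervention, high count (visits counted separately, full 12 months): 1 + 12/2 + 12/2 = 13.
- Control: 1.
- Ratio if only implementer contacts feed the log: 6:1 to 13:1.
- Ratio if the 4 research visits also feed it: (6+4)/(1+4) = 2.0 to (13+4)/(1+4) = 3.4.

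**Apparent risk ratio with equal true morbidity.** Let p be the chance that a contact leads to a logged referral, and k the number of contacts. The chance of at least one logged referral is 1 − (1 − p)^k, and the apparent ratio is [1 − (1 − p)^k_int] / [1 − (1 − p)^k_con]. The document gives no p; 2% to 10% is an assumption.

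| p | Implementer contacts only (6 or 13 vs 1) | With 4 research visits (10 or 17 vs 5) |
|---|---|---|
| 2% | 0.114 or 0.231 vs 0.020: 5.71 or 11.55 | 0.183 or 0.291 vs 0.096: 1.90 or 3.03 |
| 5% | 0.265 or 0.487 vs 0.050: 5.30 or 9.73 | 0.401 or 0.582 vs 0.226: 1.77 or 2.57 |
| 10% | 0.469 or 0.746 vs 0.100: 4.69 or 7.46 | 0.651 or 0.833 vs 0.410: 1.59 or 2.03 |

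The apparent ratio is therefore about 4.7 to 11.6 if only implementer contacts count, and about 1.6 to 3.0 if research visits also feed the log. If the comparison is restricted to referrals made at the research visits, scheduled contacts are equal (4 vs 4, ratio 1.0) wherever those visits take place.

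**Burkina Faso.** Items {6b} and {13} describe 3-monthly research contact without a site limit, while footnote b restricts the 3-monthly micronutrient and malaria rows to Kenya. If the footnote means that no such visits occur in Burkina Faso, its controls have no scheduled counselling or assessment contact in Table 1 from the group session (January to February 2022) until endline (from January 2023), about 11 months. There the first column of the table would apply.

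**The case against.** The strongest reply is that item {22} may simply describe logging of the referrals in item {6b}. That is the only referral procedure in the document, and it belongs to a team that sees both arms on one schedule. Nothing says that garden leaders or CHVs refer children. If so, ascertainment is balanced wherever the visits happen. This reading is possible, but it sits badly with the text: item {22} names the implementation teams, and items {6b} and {16c} use that term for people other than the research team and field agents.

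It can also be said that a condensed article leaves forms and recall periods to the full protocol. That is fair for those details. But the article does state who records referrals, and the allocation it states is the problem.

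Four stronger readings are tempting, and the document does not support them:
- **That referrals are the only harms record.** The next sentence of item {22} captures reasons for loss to follow-up, including deaths, and clinical malaria is a secondary outcome.
- **That harms cannot be compared between arms at all.** Deaths and losses carry no arm restriction, and referrals from the common research visits would be comparable. The article also states no between-arm analysis of referrals, so the bias bites only if someone makes that comparison.
- **That logged referrals will differ about 10-fold.** This needs logging in strict proportion to contacts and no contribution from research visits. Neither is stated.
- **That nobody reviews the log.** Item {23} describes the bi-weekly review thus: "This includes the review of adherence to intervention components, logistical aspects, feedback from beneficiary households, completeness and quality of collected data, and adherence to milestones". The list is not exhaustive and covers data completeness, and data managers also report to the steering committee (item {21a}). That referrals are not named does not show that they go unreviewed.

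**Conclusion.** The point stands in a limited form. As written, the referral log belongs to staff with about 6 to 13 scheduled contacts per intervention household against 1 per control household, and the protocol does not say that research-visit referrals enter it. Counts from this log are likely to be ascertained unequally, in the direction of apparent harm from the intervention. The problem is greatest in Burkina Faso if footnote b means that the common visits are not held there.

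The contact counts follow from the schedule. The risk ratios (about 4.7 to 11.6 without research visits in the log, 1.6 to 3.0 with them) rest on an assumed 2% to 10% chance of logging per contact and on equal true morbidity, so they illustrate the bias and do not predict it. The conclusion also rests on reading the implementation teams as delivery staff, which items {6b} and {16c} support but item {22} does not spell out. It is worth correcting because the remedy is cheap.

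**What to change.** Amend item {22} as follows:
- The research study team records referrals, reasons for referral and vital status on one identical form in both arms, at the contacts common to both: endline at both sites, and the 3-monthly visits where they are held.
- The source of each referral is recorded.
- Any between-arm statement on harms uses only the data from these common contacts. Events noted by garden leaders or CHVs are listed separately.

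Reconcile items {6b} and {13} with Table 1 footnote b, so that it is clear which research contacts take place at each site.

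The cost is a wording amendment, one form added to contacts already planned, and slightly longer visits. The change concerns record-keeping only and alters no referral or care procedure.
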